### 2.5. Outcome measures

The diagnosis questionnaires and cognitive evaluation tools are used to analyze the associations between the RAT results and the clinical problems seen in children with ADHD. Through these diagnosis questionnaires and cognitive evaluation tools, information on externalization problems, impulsivity and hyperactivity, inattention, and WM in children with ADHD will be collected.

#### 2.5.1. Diagnosis questionnaires

##### 2.5.1.1. Korean version of the child behavior checklist

The child behavior checklist (CBCL) is a standardized child behavior assessment tool that allows parents to evaluate various aspects of child behavior based on their observations (Achenbach, 1991). In this study, the Korean version of CBCL (K-CBCL) will be used (Oh et al., 1997). The K-CBCL is a parent-report questionnaire with 121 items providing data on various emotional and behavioral problems found in children (Park et al., 2014). The K-CBCL is composed of a social functioning scale and problematic behavior scale. The social functioning scale includes socialization, academic functioning, and total social competence. The problematic behavior scale includes subscales of Withdrawn, Somatic complaints, Anxious/Depressed syndrome, Social problems, Thought problems, Attention problems, Delinquent behavior, Aggressive behavior, Internalizing symptoms, Externalizing symptoms, Total score, Sexual problems, and Emotional Lability. For each item, parents measure child’s behaviors on a three-point scale as follows; they check “0” if their child has never shown the specific behaviors; check “1” if their child shows the behavior somewhat or sometimes; and check “2” if the specific behavior is observed very often. The raw scores for each subscale are calculated by summing the scores obtained from each item, and they are converted to a T score.

##### 2.5.1.2. Disruptive behavior disorder scale

The disruptive behavior disorder scale (DBDS) is a psychiatric assessment scale based on the DSM-IV diagnostic criteria to rate attention deficit/hyperactivity disorder (ADHD), oppositional defiant disorder (ODD), and conduct disorder (CD) (Silva et al., 2005). The Korean version of DBDS will be used for assessment of the disruptive behavioral symptoms of the participants (Kim, 2002). The scale consists of 41 items, including 18 items asking about ADHD symptoms, eight questions about ODD symptoms, and 15 questions about CD symptoms. Each item is calculated on a four-point Likert scale of “0” for “not at all,” “1” for “just a little or sometimes,” “2” for “pretty much or quite often,” and “3” for “very much.” Clinical symptoms were considered if they met the criteria of DSM-IV, at least six of the nine inattentive and/or hyperactive/impulsive symptoms, four of the eight oppositional defiant behaviors, and three of the 15 conduct behaviors (Park et al., 2013).

##### 2.5.1.3. Inattention/overactivity with aggression conners rating scale

The inattention/overactivity with aggression (IOWA) conners rating scale is one of the widely used measures to evaluate the therapeutic effectiveness of ADHD children and has the advantage of being reliable in evaluating various externalizing behaviors such as aggression and rebellious behaviors in ADHD children as well as hyperactivity (Shin et al., 2005; Waschbusch and Willoughby, 2008). The IOWA Conners Rating Scale consists of 10 items about inattentive, impulsive, and overactive (IO) symptoms and oppositional defiant (OD) symptoms. The first five items compose the IO subscale, and the other five items compose the OD subscale. Within the IO subscale, three items measure hyperactivity and impulsivity, and the remaining two measure inattentiveness (Waschbusch and Willoughby, 2008). Each item is calculated using a four-point Likert Scale with “0” for “not at all,” “1” for “just a little,” “2” for “pretty much,” and “3” for “very much.” Total sum of the scores for each questionnaire is calculated and interpreted as the severity of clinical symptoms. Korean version of IOWA Conners rating scale was applied in this study (Shin et al., 2005).

##### 2.5.1.4. Korean version of ADHD rating scale-IV

Korean version of ADHD rating scale-IV (K-ARS-IV) will be used to identify the severity of ADHD symptoms for each participant. The original scale was developed by DuPaul (1991) based on the diagnostic criteria of ADHD described in DSM-IV, and it has been probed that Korean version has high reliability and validity to discriminate and identify the children with ADHD (Kim et al., 2003). The scale is consisted of 18 questionnaires. Parents of participants will rate each questionnaire from 0 to 3, based on the frequency of the children’s problematic behaviors over the past 6 months. The total sum indicates the severity of ADHD symptoms, and the cut-off score for ADHD criteria is 19 for total sum score.

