## 2. Methods

### 2.1. Study design

Randomized crossover trials, clinical experiments in which participants are assigned randomly to a sequence of treatments and each participant serves as one’s own control in estimating treatment effect (Senn, 2002; Piantadosi, 2005), will be used in the present study. Participants will be assigned randomly to either rhythm training followed by cognitive training or cognitive training followed by rhythm training (Figure 1). For both groups, pre- and post-training evaluations will be administered immediately before training and after the 4th week of training. Participants will have a 4-week washout phase between trainings to minimize a possible carryover effect (Senn, 2002; Piantadosi, 2005). Pre- and post-training evaluations will include diagnosis questionnaires, cognitive evaluation tools, and resting EEG measurement.

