### 2.2. Procedure

Before the start of the experiment, the participants and their parents will be provided both oral and written information regarding the purpose of the study and will provide written informed consent. Each participant will be randomly assigned to one of two groups and will undergo pre- and post-training evaluations immediately before and after the 4-week training period. In the evaluation session, the participants will proceed in the order of diagnosis questionnaires, cognitive evaluation tools, and EEG recordings. In the training session, participants will undergo a 4-week RAT or a cognitive training program. The program will be conducted five times a week, with each session lasting 30 min per day. After a 1-month washout period, the training session schedule will be switched between the two groups.

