### 2.7. Statistical analysis

All statistical analyses will be conducted using SPSS statistical software (version 24.0, SPSS, Inc., Chicago, IL, USA). The study will undertake a comparative analysis of two intervention sequences and investigate the existence of carry-over effects. This will involve conducting *t*-tests on the change of each sequence for all crossover endpoints (Wellek and Blettner, 2012; Jones and Kenward, 2014). For variables that do not show significant carry-over effects, we will compare the changes during specific interventions in both sequences. For variables that show significant carry-over effects, we will compare the changes in specific interventions during the first period. To confirm the normal distribution of the data, we will analyze the skewness and kurtosis and perform the Shapiro-Wilk and Kolmogorov–Smirnov tests. Firstly, the differences between rhythmic sequences will be compared using repeated measures ANOVA (RMANOVA) and the Bonferroni correction for pairwise comparisons. If the data do not satisfy a normal distribution, Friedman’s test one-way analysis of variance (ANOVA) will be performed. Secondly, Pearson’s correlation test will be used to calculate the correlations between RAT performance and behavioral outcome measures. Thirdly, differences of EEG band activities between the types of rhythmic sequences and the tasks will be compared using RMANOVA with Bonferroni correction. Lastly, comparisons between interventions will be performed using a two-tailed *t*-test or Mann–Whitney U test depending on normality.

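### K-ARS-IV looks back 6 months but is scheduled before and after 4-week trainings, so its change score is heavily diluted

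*Protocol article*

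**What the plan says.** Section 2.5.1.4 states that the K-ARS-IV "will be used to identify the severity of ADHD symptoms for each participant". Parents score 18 items by the frequency of "problematic behaviors over the past 6 months", and a total of 19 is the cut-off for ADHD. The scale is listed under Outcome measures (2.5), among the Diagnosis questionnaires (2.5.1).

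Section 2.1 says: "Pre- and post-training evaluations will include diagnosis questionnaires, cognitive evaluation tools, and resting EEG measurement." It makes no exception for any questionnaire. On timing, it says that "pre- and post-training evaluations will be administered immediately before training and after the 4th week of training"; section 2.2 agrees that each participant "will undergo pre- and post-training evaluations immediately before and after the 4-week training period". Each training lasts 4 weeks. Between the two, section 2.1 says: "Participants will have a 4-week washout phase between trainings to minimize a possible carryover effect." Section 2.2 calls the same gap 1 month.

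Section 2.7 sets the treatment comparison: "For variables that do not show significant carry-over effects, we will compare the changes during specific interventions in both sequences." Variables with significant carry-over are compared on first-period changes only. The fourth hypothesis in the Introduction is that behavioural outcome measures differ by intervention type.

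**The concern.** A before-and-after change informs about a 4-week training only if the second rating describes mainly those 4 weeks and the first describes mainly the time before them. A 6-month recall window does neither. Most of what the parent is asked to consider at the post-training rating is the same stretch of time already rated at the pre-training one.

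At stake is how a K-ARS-IV result would be read. The trial hopes to support rhythm training for behavioural symptoms of ADHD, and this scale gives a total ADHD symptom severity score. A flat change could mean that neither training works, or only that the instruction asked about the wrong period. The data could not tell these apart.

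**Working it through.** The plan gives no figure on this point to reproduce, so the check is one of calendar overlap.

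**Inputs.** Recall window W = 6 months (2.5.1.4), taken as 26 weeks, with 24 weeks as a sensitivity case. Training 4 weeks (2.2). Washout 4 weeks (2.1). Evaluations therefore fall at weeks 0, 4, 8 and 12, and the window of a rating at week t runs from t − W to t.

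**What each rating covers (weeks, W = 26).**

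| Rating | Window | Pre-study | First training | Washout | Second training |
|---|---|---|---|---|---|
| Period 1 pre | −26 to 0 | 26 | 0 | 0 | 0 |
| Period 1 post | −22 to 4 | 22 | 4 | 0 | 0 |
| Period 2 pre | −18 to 8 | 18 | 4 | 4 | 0 |
| Period 2 post | −14 to 12 | 14 | 4 | 4 | 4 |

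- Share of a post rating that is its own training: 4/26 = 15.4% (W = 24: 4/24 = 16.7%).
- Overlap of pre and post windows within a period: (26 − 4)/26 = 84.6% (W = 24: 20/24 = 83.3%).

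**Change scores under plain averaging (assumption).** Let S[a, b] be mean severity over weeks a to b. Time common to both windows drops out of the difference:

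- Period 1 change = (4/26) × (S[0, 4] − S[−26, −22])
- Period 2 change = (4/26) × (S[8, 12] − S[−18, −14])

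If severity before the study was stable and the training effect is present for all 4 weeks, each change equals 4/26 of that effect. The protocol gives no expected effect, so a range is assumed, with the SD of the rating held fixed:

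- 0.3 SD × 4/26 = 0.05 SD
- 0.5 SD × 4/26 = 0.08 SD
- 0.8 SD × 4/26 = 0.12 SD

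**Does the first training leak into the second-period comparison?** Weeks 0 to 8, meaning the whole first training and the washout, lie in both period 2 windows. The period 2 baseline rating is therefore not an untreated one. Under averaging, however, those weeks cancel from the period 2 change, as the second formula shows. They matter only if the first effect persists into weeks 8 to 12.

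**Does the first-period fallback help?** It removes the overlap with the other training. It leaves the dilution, because the period 1 post window is still 22/26 (85%) pre-study.

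**Check of a shorter window.** With W = 4, the windows are −4 to 0, 0 to 4, 4 to 8 and 8 to 12. Each post rating is 100% its own training, the period 2 pre rating covers only the washout, and no windows overlap.

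**The case against.** The strongest reply is that the K-ARS-IV may not be meant as a change endpoint. Section 2.5.1.4 describes it as identifying severity and gives a diagnostic cut-off. Section 2.5 says the questionnaires serve to relate RAT results to clinical problems, a use that a long window harms far less. Section 2.7 does not list its crossover endpoints. Nor is the pre/post sentence literal for every tool: the K-WISC-IV is among the cognitive tools, yet its IQ scores are for screening. This leaves real ambiguity, but it does not remove the point. For the IQ scores the protocol states the screening use, whereas for the K-ARS-IV it states no restriction, and section 2.1 repeats the diagnosis questionnaires without exception.

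A second reply is that parents weight recent behaviour. That is plausible, and it makes 15% a calendar share rather than a measured attenuation. The score then depends on parents departing from the instruction to an unknown degree.

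A third is that other outcomes remain. This stands, and it limits the harm. The K-ARS-IV is one of four questionnaires; the sections on the other three state no 6-month window, and the cognitive tests and EEG are untouched. The distortion is also mainly toward no difference, so it is not a route to a false benefit.

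A reader might go further and infer that carry-over is built into the second-period comparison because its ratings span both trainings. The documents do not support this: the plan analyses changes, and the shared weeks cancel under the same averaging that produces the 15%. An effect outlasting the washout would not cancel, but that requires a persisting effect, which the recall window does not create.

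**Conclusion.** The point holds as one of dilution. On the protocol's own schedule, about 15% of each post-training K-ARS-IV rating is its own training (17% with 24 weeks), and about 85% of the window is shared with the pre-training rating (83%). These shares need only the conversion of 6 months to weeks. The step to 0.05 to 0.12 SD needs more: plain averaging by parents, stable severity before the study, an effect present throughout training, an unchanged SD, and assumed true effects of 0.3 to 0.8 SD. If recent weeks count for more, the loss is smaller by an amount the protocol gives no means to estimate.

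A null K-ARS-IV change would therefore be close to uninformative about either training. This should be fixed, but it does not threaten the trial as a whole: it affects one symptom measure that is not named as primary.

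**What to change.** **Preferred.** State in 2.5.1.4 that the 6-month form, with its cut-off of 19, is used for screening and baseline severity only, and exclude it from the crossover change endpoints in 2.7. Read symptom change from the other questionnaires already in the plan (IOWA Conners, DBDS, K-CBCL), after confirming that their recall windows fit 4-week periods; the protocol does not state those windows. The cost is a sentence or two and one fewer change endpoint.

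**Alternative.** Instruct parents to rate one identical window of at most 4 weeks at all four evaluations. The cost is a changed instruction line, but scores are no longer comparable with the 6-month norms or cut-off, and the reliability and validity cited for the Korean version may not carry over. This route is open only before ratings are collected, because a rating cannot be re-taken later for a different window.

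A longer washout is not a substitute. To clear the first training it would have to last about 22 weeks for the period 2 post window (26 − 4) and 26 weeks for the period 2 pre window, and the dilution within each period would remain.

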#### 2.5.2. Cognitive evaluation tools

##### 2.5.2.1. Korean version of the wechsler intelligence scale for children: 4th ed.

The Korean version of the wechsler intelligence scale for children: 4th ed. (K-WISC-IV) was used to assess the intellectual and cognitive abilities of the children. The Wechsler intelligence scale is the most widely used tool to assess the intellectual functioning of children and adolescents, and the Korean version was standardized on a sample of 2,448 Korean children, aged from 6–16 years (Kwak et al., 2011). The K-WISC-IV consists of 10 core subtests and five supplemental subtests. The full-scale IQ score (FSIQ) is calculated by the core subtests; using the composite of two or three core subtests, four main indices are calculated: the verbal comprehension index (VCI), perceptual reasoning index (PRI), working memory index (WMI), and processing speed index (PSI). In this study, IQ scores were used for screening the participants, and the digit span (DS) and the letter-number sequencing (LN), which is a subtest of the working memory index. The DS consists of digit span forward (DSF) and digit span backward (DSB) tests. Participants will recall a spoken sequence of numbers in the same order as they were presented (DSF) and in inverse order (DSB). The LN task asked participants to listen to a sequence of numbers and letters arranged in a random order and to recall the numbers in ascending order and then the letters in alphabetical order.

##### 2.5.2.2. Stroop color and word test children’s version

Stroop color and word test (SCWT) is a neuropsychological assessment tool for evaluating the efficiency of the prefrontal lobe, especially attentional and executive functioning (Golden and Golden, 2002). This tool is frequently used for evaluating cognitive inhibition in children (Archibald and Kerns, 1999). The SCWT is composed of three subtest conditions of word, color, and color-word. In the first subtest, word condition, participants should read and speak the colored words printed in black ink. In the color subtest, participants were asked to read the bar of X’s, colored in red, blue, or green ink. Last, in the color-word subtest, colored words are printed a color incongruent with the printed name. Participants should ignore the letter and read the printed ink sequentially as in other subtests. For each subtest, participants should read the stimulus as quickly and accurately as possible within 45 s, and the raw scores will be scored according to the number of correct answers. Interference score is calculated as the difference between the color score and the color-word score. In the current study, the Korean version of SCWT was conducted through the E-Prime software (Psychology Software Tools, Pittsburgh, PA, Version 3.0).

##### 2.5.2.3. Children’s color trails test

The children’s color trails test (CCTT) is a neuropsychological test that can evaluate frontal lobe function of child psychiatric disorders, including attention and executive function (Koo and Shin, 2008). Based on the adult version of the trail making test (TMT), the child’s version minimizes the disadvantages caused by age by avoiding dependence on letters and minimizes the influence of culture and language using colors and numbers instead of letters (Williams et al., 1995). The Korean version of standardized CCTT (Koo and Shin, 2008) was conducted during the study. The test consisted of two subtests: CCTT-1, which measures sequential processing power and psychomotor speed, and CCTT-2, which examines continuous divisional attention and cognitive flexibility (Reum et al., 2021). Under the researcher’s instruction, participants performed each subtest in consecutive order, performing a practice task prior to the actual task. In the first subtest, CCTT-1, participants should connect the numbers 1–15 as quickly and correctly as possible, without lifting the pencil from the paper. For the next subtest, CCTT-2, identical numbers are embedded in separate pink and yellow circles. Participants should connect the numbers sequentially from 1 to 15, alternating between colored circles. The raw score is calculated as the time for completing each task, and the number of errors committed was counted for ascending numbers or altered colors.

##### 2.5.2.4. Advanced test of attention

In this study, we will use the advanced test of attention (ATA), a computerized continuous performance test (Shin et al., 2000) to assess participants’ inattention and inhibitory control. The test consists of visual and auditory tasks. A total of three non-verbal stimuli will be presented randomly during each visual and auditory task, all of which were non-target except for one stimulus. Participants should press the button for the target stimuli as fast as possible, and not respond to the non-target stimuli. For the visual task, an image with a black triangle inside the colored square will be the target stimulus, and for the auditory task, three consecutive beep sounds will be a target stimulus. Each task will be implemented after the practice trial with the researcher. The test will be measuring four main variables: (1) omission error which measures the symptoms of inattention, (2) commission error which measures impulsivity and disinhibition, (3) mean time for correct responses which measure the processing speed, and (4) standard deviation of response time which measures the consistency of attention. Based on normative distribution according to age and gender, all scores will be translated into T scores with average of 50 and standard deviation of 15. In addition, two variables will be also collected: (1) d’ variable to measure whether participants discriminate target stimuli with non-target stimuli well, and (2) Beta (β) to measure the participants’ response bias whether there are more omissions or commissions in the event of error responses. The visual and auditory tasks each lasting 15 min.

##### 2.5.2.5. Comprehensive attention test

The comprehensive attention test (CAT), a Korean version of a computerized continuous performance task will be administered (Yoo et al., 2009). For each selective task, participants will be instructed to make the response to target stimuli and inhibit the response to non-target stimuli. Participants’ performance will be assessed by four main variables: (1) omission errors to measure inattention, (2) commission errors to measure impulsivity, (3) response time to measure the processing speed, and (4) response time standard deviation to measure the variability of the response time. All raw scores will be standardized into attention quotients (AQs), adjusted for age and gender by comparison with a normal population, and the average AQ is 100 with standard deviation of 15. In addition, two variables will be also collected: (1) d’ variable to measure whether participants discriminate target stimuli with non-target stimuli well, and (2) Beta (β) to measure the participants’ response bias whether there are more omissions or commissions in the event of error responses. The visual and auditory selective tasks each lasting 11 min.

Phase locking value analysis has been widely used as a robust method for quantifying functional connectivity between brain regions (Lachaux et al., 1999; Mormann et al., 2000; Wang et al., 2020). Compared to visual WM, which has been studied extensively, auditory WM has not been studied as well, and the results are unclear. Several studies have shown theta synchronization as a visual and auditory WM marker (Knyazev, 2007; Düzel et al., 2010; Albouy et al., 2017). In typically developing adults, connectivity in the theta frequency band increases between frontal and parietal regions (Albouy et al., 2017) and between prefrontal and mediotemporal regions (Fell et al., 2008; Fell and Axmacher, 2011) during auditory WM tasks. During the RAT, specifically the maintenance and reproduction tasks, we expect increased connectivity between frontal and parietal and between frontal and medio-temporal regions in the theta band in children with ADHD.

